**Table 1 Tab1:**
[figure not shown]
Assessment schedule for clinical study with the medical device

### Blinding

Patients and ward nurses will not be entirely blinded after group allocation due to the nature of the interventions. Despite this, participants will not be directly informed of their group allocation in terms of usual care or intervention, and the ward nurses will only be informed about the broad purposes of the research [41]—the study of a new double-chamber syringe for intravenous administration and flushing. In contrast, research nurses from the team outside the orthopaedic department will be blinded when rating some of the main outcomes such as phlebitis and infiltration. In accordance, external data analysts involved in the study will also be blinded to patient allocation and treatment groups.

### Interventions

The research/ward nurses will collect baseline personal (e.g. age, sex) and clinical data (e.g. intravenous medication prescribed, other medication, medical history). Data about the catheterization process includes date and time of catheter insertion, antiseptic used, catheter size, drugs injected, site of the insertion, dressings and devices used, skin assessment or vein visibility, as well as pain related to catheter insertion as reported by the patients. Ward nurses will receive a brief educational session focused on the flushing procedure during intravenous drug administrations and aseptic principles in order to ensure standardization of all the clinical procedures during the clinical research.

The study protocol ensures that there is no selection bias, i.e. the participants in both groups received the same treatments/care, with the exception of the manipulated variable. Thus, the two groups only differ in the syringes used to perform the intravenous medication administration and flushing procedures. In arm A, nurses use the double-chamber syringe and the traditional syringes will be used in arm B. Several aspects regarding the catheterization, medication administration, and monitoring of the PICV will be ensured to be equal in both groups and in agreement with Good Clinical Practices.

The catheterization in both groups will be done according to the standard procedures of the aseptic technique [17, 19, 30, 42]. In both arms, the decision to change the PIVC will be based on clinical criteria, such as completion of therapy, phlebitis, infiltration, occlusion, accidental removal, or suspected infection [16, 19, 23, 43–45]. In fact, several studies indicate that the routine replacement of PIVCs (using predetermined time frames, e.g. 72–96 h) does not show advantages when compared to clinically indicated replacements [44–46]. Previous to the administration of the intravenous medication, vein permeability will be assessed and the pulsatile (push–pause) delivery action will be used to optimize flush outcomes and minimize damage to the vein [31, 33, 36]. All medication safety precautions inherent to intravenous medications will be followed when administering flush solutions. Any deviations from the protocol will be recorded.

Outcome assessment visits will be performed on a daily basis, in accordance with each participant’s period of prescribed intravenous drug administration. Using the same procedures in both groups (warranting the internal validity of the study), two distinct approaches will be considered (Table 1): (i) *unblinded visits* (always, at the time of the intravenous administration)—due to the nature of the interventions with the medical device, the wards nurses are aware of the participant allocation; (ii) *blinded visits* (once a day, outside the routine periods for drug administration by the ward nurses)—the research nurses are not aware of participant allocation and therefore there is no risk of distorting outcome measurements.

The *unblinded visits* will be performed by the ward nurses when the intravenous medications are administered (Table 1, type 4 visits). At this moment, the outcomes assessed will be phlebitis [47], infiltration [48], occlusion, catheter and insertion site analysis (main outcomes), as well as other reasons for catheter removal, maintenance time of the catheter, insertion attempts, and total number of catheters used (secondary outcomes; if applicable, i.e. when there is a need for new catheterization). The *blinded visits* will be performed by a research nurse who evaluates some of the main outcomes, namely phlebitis, infiltration, and catheter and insertion site analysis (Table 1, type 5 visits).

The last unblinded visit for outcome assessment will be performed at the end of the intravenous therapy by the ward nurse that removes the PIVC (Table 1, type 6 visits). During this visit, all the outcomes will be assessed by the ward nurses, with the exception of the insertion attempts and patient satisfaction. After the completion of the intravenous therapy and PIVC removal (Table 1, type 7 visits), research nurses will conduct a blinded visit similar to the previous type 5 visits. However, research nurses will also assess patients’ satisfaction about the clinical treatment. Finally, a follow-up assessment will be done (48–72 h after visit number 7) for the main outcome phlebitis (Table 1, visit 8). Throughout the study period, regardless of the type of visit, all adverse events will be assessed and recorded.

### Outcomes

The main primary outcomes are the catheter-related complications, such as vascular trauma (phlebitis and infiltration) and occlusion. Specific scales for phlebitis [47] and infiltration [48] assessment will be used and data analysed in terms of mean scores, standard deviations, and proportions. The occlusion will be rated by the ward nurses on the participants’ case report forms (CRFs) and analysed as proportions.

The secondary outcomes involve other reasons for catheter removal (e.g. accidental dislodgment), maintenance time of the catheter, number of syringes and catheters used during the intravenous treatment, catheterization attempts, nurses’ perception about risk and safety, as well as the satisfaction of the participants. The reasons for catheter removal are reported on the CRF and treated as proportions. The maintenance time of the catheter, number of syringes and catheters used, and catheterization attempts are also identified on the CRF, being analysed through mean scores and standard deviations.

Ward nurses’ and patients’ satisfaction about the clinical treatment will be rated using questionnaires focused on essential risk and safety features, in a five-point Likert scale, developed and validated by the research team for this purpose. These scores will be analysed through mean scores and standard deviations.

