### Sample size

Commonly, the sample size calculation is based on an expected incidence of the primary outcome. In our study, we have several primary outcomes regarding PIVC-related complications. Therefore, the sample size was calculated considering the lower prevalence value in Portuguese contexts for one of the primary outcomes (namely occlusion, with a 19% prevalence rate) [13, 28]. Also, the sample size determination was established using G*Power software, taking into consideration the type I (α) error level, the statistical power (type II error, β), and the standard deviation of the measurement for continuous outcomes. Fisher’s exact test comparing the proportions in two groups (*p* control = 0.19; *p* experimental = 0.05) are considered (Table 2). Ensuring a type I error of 5% and a statistical power of 80%, the estimated sample size is 146 participants (73 participants in each group).

**Table 2 Tab2:** Sample size estimation

Input		Output	
Tail(s)	One	Sample size group 1	73
Proportion p1	0.19	Sample size group 2	73
Proportion p2	0.05	Total sample size	146
α err prob	0.05	Actual α	0.0197
Power (1-β err prob)	0.80		
Allocation ratio N2/N1	1		

Fisher’s exact test: Proportions, inequality, two independent groups

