### Data collection, management, and analysis

Paper CRFs will be used in this clinical study to record all the information required from the protocol. Distinct CRFs will be used for the blinded and unblinded nurses. All CRF data are anonymized for subsequent analysis and reports/publications. According to this, study participants will be assigned a unique subject identification (ID) number. Study subject ID numbers will be used on all data collection instruments. The names of the participants on the consent forms will be stored separately from CRFs in locked cabinets and only accessible by named personnel.

Data to be collected include individual characteristics, demographics, and clinical information. No biological specimens will be collected. Data will be entered and analysed using the Statistical Package for the Social Sciences, version 24 (IBM SPSS Statistics 24, SPSS Inc., Chicago, IL, USA). Baseline characteristics of patients and catheters will be described by group. Means, standard deviations, frequencies, and percentages will be used as descriptive statistics. For each group, the number of participants who were randomly assigned will be analysed for the outcomes. Data analysis will be done using intention-to-treat principles [49]. Missing data will be handled using the last observation carried forward method, which uses the last available data for each trial participant, at the visit prior to withdrawal from the study, in the data analysis [50]. Specifically, for each primary and secondary outcome, the estimated effect size and its precision will be analysed. Baseline data for both groups will be observed to check for similarity in important variables. According to these results, variables with statistically significant differences between groups will be controlled in subsequent outcome analyses. The primary and secondary outcomes in the two groups will be examined to detect the effect of group allocation on each condition. Specifically, differences between continuous variables will be analysed using Student’s *t-*test. For skewed data, median values and interquartile ranges will be calculated and undergo nonparametric analysis using Mann-Whitney *U* test. Categorical variables will be compared by χ^2^ test or Fisher’s exact test, as appropriate. We deemed *p* values less than 0.05 to be significant (two-sided significance level of 5%). No additional analyses (e.g. interim analyses, planned subgroup analyses) will be performed.

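### At least three primary outcomes are each judged at an unadjusted two-sided 5% with no success rule, so the stated 5% type I error covers one occlusion test only

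*Protocol article*

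**What the plan says.** - **Which outcomes are primary.** The Outcomes section states: "The main primary outcomes are the catheter-related complications, such as vascular trauma (phlebitis and infiltration) and occlusion". The Sample size section confirms the plurality: "In our study, we have several primary outcomes regarding PIVC-related complications". The Objectives section gives the same three (phlebitis, infiltration, occlusion) as a closed list. The description of the unblinded visits under Interventions adds another: "occlusion, catheter and insertion site analysis (main outcomes". The blinded-visit description also counts this item among the main outcomes.
- **How each is analysed.** For two of them: "Specific scales for phlebitis [47] and infiltration [48] assessment will be used and data analysed in terms of mean scores, standard deviations, and proportions". For the third: "The occlusion will be rated by the ward nurses on the participants’ case report forms (CRFs) and analysed as proportions".
- **Who rates them.** Under Interventions, phlebitis and infiltration are rated both by unblinded ward nurses and by blinded research nurses. Occlusion is rated by ward nurses only.
- **Significance.** Under Data collection, management, and analysis, the primary and secondary outcomes are all compared between groups, and p values below 0.05 are deemed "to be significant (two-sided significance level of 5"%). No order, composite, alpha split or requirement that all outcomes succeed is given.
- **Error rate claimed.** The Sample size section and Table 2 give a type I error of 5% and 80% power for one one-tailed Fisher test on occlusion (0.19 versus 0.05), with 73 per group.

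**The concern.** The trial is meant to establish the effectiveness and safety of a new device, yet the protocol does not say which result would establish it. With several primary outcomes, each tested at 5%, a significant difference on any one could be reported as the primary finding. The 5% in the Sample size section gives no protection against that, because it is the alpha of one test. Two choices widen the room further: score or proportion for phlebitis and infiltration, and blinded or unblinded ratings for the same two. At stake is a device claim with a false-positive risk above the stated 5%, and an analysis that can be chosen after the data are seen.

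**Working it through.** **Inputs from the protocol.** Three named primary outcomes; two-sided 0.05 per p value; chi-square or Fisher for proportions; 73 per group; occlusion rates 0.19 and 0.05. **Assumptions.** Any one significant primary outcome counts as success; the correlations below; where exact test sizes are used, a common event rate for all three outcomes.

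**1. The plan's own figure.** Enumerating a one-sided Fisher test at alpha 0.05 over two binomials with rates 0.19 and 0.05, the smallest n with at least 80% power is 73 per group (power 0.8003). Its actual alpha at a common rate of 0.05 is 0.0197. Both match Table 2, so the stated 5% is the nominal level of one occlusion test.

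**2. Three tests at full size, independent.** 1 − (1 − 0.05)³ = 1 − 0.8574 = 14.3%.

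**3. Three tests at full size, correlated** (simulated two-sided z tests):

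| Assumed correlation | At least one false positive |
|---|---|
| 0 | 14.3% |
| 0.3 | 13.6% |
| 0.5 | 12.5% |
| 0.7 | 10.9% |
| 0.9 | 8.4% |

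**4. Actual size of the tests at 73 per group**, three independent binary outcomes:

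| Common rate | Chi-square: size, familywise | Two-sided Fisher: size, familywise |
|---|---|---|
| 0.05 | 4.84%, 13.8% | 1.44%, 4.3% |
| 0.19 | 5.04%, 14.4% | 2.94%, 8.6% |
| 0.40 | 5.20%, 14.8% | 3.47%, 10.1% |

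For example, Fisher at 0.19: 1 − (1 − 0.0294)³ = 8.6%. The Sample size section says 19% is the lower prevalence value used for sizing, so the 5% row is not the protocol's own scenario.

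**5. If scores and proportions are both tested.** The count is 2 + 2 + 1 = 5. Independence would give 1 − 0.95⁵ = 22.6%, but two analyses of one scale are not independent. With an assumed correlation of 0.8 between them and independent outcomes, simulation gives 19.3%. If the outcomes also correlate at 0.5, it gives 16.8%.

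**6. What control would cost in occlusion power** (0.19 versus 0.05, 73 per group, two-sided):

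| Alpha for occlusion | Fisher | Chi-square |
|---|---|---|
| 0.05 (first in a fixed sequence) | 69.1% | 77.2% |
| 0.05/3 = 0.0167 (Bonferroni) | 50.4% | 62.1% |

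Under Bonferroni over three outcomes, two-sided Fisher needs 117 per group for 80% power. With no adjustment it needs 90. The shortfall from 80% in the first row arises because Table 2 is one-tailed while the analysis is two-sided, which is a separate matter.

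**The case against.** Five points can be made on the other side.

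- **No familywise claim is made.** The protocol does not say that 5% covers all primary outcomes, and if all three had to be significant, 5% each would need no adjustment. This stands as a condition: the inflation applies only where any one success suffices. But no such all-must-succeed rule is written, and power was computed for occlusion alone.
- **The inflation may be small.** Fisher tests are conservative, and with all rates near 5% the familywise error would be 4.3%. That is correct, but the protocol also allows chi-square and its own lowest rate is 19%.
- **Scores and proportions may only be descriptive summaries.** This is a fair reading. A reader might infer that every primary outcome is tested in more than one way and that the error is therefore 22.6%. The documents do not support this: occlusion has a proportion analysis only, two tests per scale are not expressly scheduled, and independence within a scale is implausible.
- **Sizing on the rarest outcome may cover the others.** A reader might infer that the sample size supports occlusion alone. The protocol gives no expected effect on phlebitis or infiltration, so this cannot be settled. With the same relative reduction (ratio 0.05/0.19), two-sided Fisher power at 73 per group would be 84% at an assumed 25% control rate and 91% at 30%. With a constant 14-point difference it would be 52% and 45%.
- **An analysis plan may settle the testing procedure.** It may. But the primary outcomes and a flat 0.05 rule are stated here, and the primary list differs between sections of this document.

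A reader might also take the catheter and insertion site item as a definite fourth primary outcome to be struck out. It may instead be the inspection from which phlebitis and infiltration are scored, and Table 1 is not visible. Only reconciliation can be asked for.

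**Conclusion.** The concern holds in this form. The protocol fixes at least three primary outcomes, leaves the list open and inconsistent between sections, gives two of them two forms of analysis, and judges every p value at an unadjusted two-sided 5% without a success rule. The stated 5% covers one occlusion test.

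If any one significant primary outcome counts as success, the chance of at least one false positive among three is up to about 14% for independent tests. It is 8.6% by two-sided Fisher at a 19% rate and about 11% at full size with a correlation of 0.7. Testing scores as well as proportions raises it further, by an amount that depends on unknown correlations. The correlations, the common event rates and the any-one-suffices reading are assumptions. The absence of a stated rule is not.

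**What to change.** 1. **Outcomes section:** replace the open wording with a closed list. Name one analysis per primary outcome (proportion of participants with the event) and make the mean-score analyses secondary.
2. **Outcomes and Interventions sections:** say that the blinded research nurses' ratings are the primary ones for phlebitis and infiltration.
3. **Interventions section:** reconcile the status of the catheter and insertion site item with the Objectives and Outcomes sections.
4. **Data collection, management, and analysis:** state one familywise rule at two-sided 5%. One option is a fixed sequence of occlusion (the outcome the trial is sized on), then phlebitis, then infiltration, each tested only if the one before is significant.

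**Cost.** Steps 1 to 3 are wording. The sequence in step 4 leaves occlusion at its present two-sided power but makes it the gatekeeper. Even if the design effect is true, occlusion would fail 1 − 0.772 = 23% (chi-square) to 1 − 0.691 = 31% (Fisher) of the time, and phlebitis and infiltration could then not be claimed. Occlusion is also the one named primary outcome without a blinded rating. The sponsor may therefore prefer another pre-stated order, or Holm. Holm's first step is at 0.0167, where occlusion power is 50.4% (Fisher) or 62.1% (chi-square); its power is higher only when another outcome has already been rejected. Whichever rule is chosen, the sample size should be checked against it before recruitment.

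### Catheter maintenance time is compared as a plain mean or rank although removal at the end of therapy censors it for failure, so the comparison mixes prescription length with failure and loses power

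*Protocol article*

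**What the plan says.** Maintenance time is a secondary outcome (Objectives; Outcomes). The Outcomes section groups it with counts: "The maintenance time of the catheter, number of syringes and catheters used", and then "catheterization attempts are also identified on the CRF, being analysed through mean scores and standard deviations". The section on data collection, management and analysis states that "differences between continuous variables will be analysed using" Student's t-test, and adds: "For skewed data, median values and interquartile ranges will be calculated and undergo nonparametric analysis using Mann-Whitney" U test. No time-to-event method is named there.

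Under Interventions, the decision to change a catheter "will be based on clinical criteria, such as completion of therapy, phlebitis, infiltration, occlusion, accidental removal, or suspected infection". The same section argues against routine timed replacement. Outcome visits are daily, "in accordance with each participant’s period of prescribed intravenous drug administration". Insertion date and time are recorded at baseline, and the reason for removal is recorded on the case report form.

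**The concern.** A catheter removed in working order because the prescription ended has not failed. Its failure time is known only to exceed its dwell time, so for failure it is a censored observation. The t-test and the Mann-Whitney test both treat that dwell as a completed lifetime. A catheter that serves a 2-day course without trouble therefore scores lower than one that fails on day 4 of a longer course.

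The syringe can plausibly change how often and how soon catheters fail, but not how long the drug is prescribed. The more removals are due to completed therapy, the more of the variation in dwell is prescription length. A null result could then be read as no effect on catheter durability when the test had little chance of finding one.

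**Working it through.** **Inputs from the protocol.** 73 per arm, 1:1 allocation, two-sided 5% in the analysis, catheters expected to stay at least 24 h, and occlusion 19% vs 5% in the sample size section.

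**Assumptions, not in the protocol.** Therapy length is 1 day plus a lognormal part of mean 3 days (mean 4 days; SD 0.9, 1.8 or 3.0 days), or 1 + Gamma(4,1) days (mean 5). Failure times are exponential (Weibull shapes 0.7 and 1.5 gave similar results). There is one catheter per participant. All-cause failure proportions are varied, because the protocol gives none.

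**The plan's own figure.** The protocol states no power for maintenance time. Its sample size does reproduce: a one-sided Fisher exact test with 0.19 vs 0.05 has power 0.8003 at 73 per arm and 0.7944 at 72, with actual α 0.0197. This point does not touch that calculation.

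**What is recorded.** With F the time to failure and T the end of therapy, dwell is D = min(F, T). For an exponential failure rate λ and fixed T, the mean is E[D] = (1 − e^(−λT))/λ.

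**By hand at 19% vs 5%, T = 4 days.**
- Control: λ = −ln(0.81)/4 = 0.0527 per day; E[D] = 0.19/0.0527 = 3.61 days.
- Experimental: λ = −ln(0.95)/4 = 0.0128 per day; E[D] = 0.05/0.0128 = 3.90 days.
- The hazard ratio is 0.0128/0.0527 = 0.24, a large effect, yet mean dwell differs by only about 0.3 day.

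**Approximate power at the same rates.**
- t-test, with a simulated mean difference of 0.34 day and SD about 1.8 days: z = 0.34/(1.8 × √(2/73)) = 0.34/0.298 = 1.14. Power ≈ 1 − Φ(1.96 − 1.14) = 0.21. Simulation gives 0.21.
- Log-rank: expected failures are 73 × 0.19 + 73 × 0.05 = 17.5. The Schoenfeld formula gives z = |ln 0.24| × √(17.5/4) = 2.99 and power Φ(2.99 − 1.96) ≈ 0.85. With so few events this is optimistic; simulation gives 0.76–0.79.

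**Simulated power, 73 per arm, two-sided 5%** (ranges run over the three therapy-length SDs; the 44% vs 22% row uses the 5-day Gamma model):

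| All-cause failure, control vs experimental | t-test | Mann-Whitney | Log-rank, end of therapy censored |
|---|---|---|---|
| 19% vs 5% | 0.16–0.37 | 0.19–0.26 | 0.76–0.79 |
| 35% vs 15% | 0.35–0.58 | 0.39–0.50 | 0.82–0.84 |
| 44% vs 22% | 0.52 | 0.52 | 0.84 |
| 50% vs 30% | 0.46–0.56 | 0.48–0.53 | 0.73–0.78 |
| 57% vs 35% | 0.58–0.66 | 0.61–0.65 | 0.79–0.85 |
| 70% vs 50% | 0.64–0.66 | 0.65–0.67 | 0.76–0.83 |
| 30% vs 30% (null) | 0.052 | 0.052 | 0.055 |

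In the 44% vs 22% row, mean dwell is 3.6 vs 4.3 days. Separate runs gave log-rank 0.81 at about 20% vs 5% (t-test 0.24), and t-test 0.61 against log-rank 0.74 at 68% vs 49%.

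**Share of power lost by the t-test.** At 19% vs 5%: 1 − 0.371/0.774 = 52% to 1 − 0.157/0.789 = 80%. At 44% vs 22%: 1 − 0.515/0.841 = 39%. At 70% vs 50%: 1 − 0.657/0.755 = 13% to 1 − 0.661/0.826 = 20%.

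**The case against.** The best defence is that failure is examined elsewhere. Phlebitis, infiltration and occlusion are the primary outcomes, and removal reasons are compared as proportions. In the 44% vs 22% scenario, failure versus completed therapy analysed as a simple proportion has power 0.81 by χ² and 0.76 by Fisher, close to the log-rank 0.84. Much of the signal could thus be recovered from planned data. This stands in part: the protocol names no pooled all-cause failure endpoint, single-cause comparisons would have less power, and neither repairs the comparison of time itself. Mean dwell is also a legitimate descriptive quantity, and the protocol does not say that maintenance time is meant to measure failure-free survival.

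Three stronger readings are tempting, and the documents do not support them.
- **That most of the signal is lost.** This is true only if all-cause failure is near 19% vs 5%. The protocol gives 19% for occlusion alone, as the lower prevalence among its primary outcomes. Three non-overlapping complications at 19% or more would already total 3 × 19% = 57% of control catheters, and the loss is then partial.
- **That the test is biased.** Randomisation balances therapy length on average, and the simulated type I error stays near 5%.
- **That several catheters per participant will be analysed as independent records.** Nothing says so, and the analysis section points to randomised participants as the unit.

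The Mann-Whitney fallback is not an answer. It has the same defect and nearly the same power.

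**Conclusion.** The point holds as a matter of power and interpretation for one secondary outcome. The article itself fixes an analysis that counts removals at the end of therapy as observed lifetimes. In every non-null scenario in the table, both planned tests have less power than a log-rank test that censors those removals. The loss runs from roughly 13% of the power when 70% of control catheters fail to about 80% at 19% vs 5% with widely varying therapy lengths. Where the trial would fall in that range cannot be settled from the documents, which give neither the all-cause failure share nor therapy length. The figures rest on the assumed therapy lengths, the assumed failure shapes and one catheter per participant. The sample size and the primary comparisons are unaffected.

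**What to change.** Define the analysed quantity as time from insertion to failure of each participant's first catheter, with removal at completion of therapy as censoring. Compare arms by Kaplan-Meier curves with a log-rank test or Cox model. For individual failure causes use cumulative incidence, since other failures compete. Keep mean/SD or median/IQR of dwell as description only. Using the first catheter gives one record per participant.

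The change is one of wording, made before analysis. Insertion time, maintenance time and removal reason are already collected, and no participants or procedures are added. The cost is slightly more analysis work and a change in what the outcome measures, from total dwell to failure-free catheter time, which should be stated openly.

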## Methods/design

### Objectives

The main objective is to establish the clinical effectiveness and safety parameters of the new medical device: a double-chamber syringe for intravenous administration and flushing. In order to accomplish this objective, the main outcomes measured are related to PIVC complications, namely vascular trauma (phlebitis and infiltration) and occlusion. The secondary outcomes are related to the catheters (such as other removal causes, maintenance time, insertion attempts, and the number of catheters needed to achieve the prescribed intravenous treatment), but also explore patient’s satisfaction of the intravenous treatment received, as well as nurse’s satisfaction with the medical device (including the perception of safety/risk).

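### The planned two-group tests for the nurse-reported outcomes ignore the nurse, who is not randomised and very probably uses both syringes

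*Protocol article*

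**What the plan says.** **What is measured.** In the protocol article, Objectives includes "nurse’s satisfaction with the medical device (including the perception of safety/risk" among the things to be explored. Outcomes lists as secondary outcomes "nurses’ perception about risk and safety, as well as the satisfaction of the participants", and says that ward nurses' and patients' "satisfaction about the clinical treatment will be rated using questionnaires focused on essential risk and safety features", on a five-point Likert scale. On analysis, that section adds only: "These scores will be analysed through mean scores and standard deviations".

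**How it is compared.** Data collection, management, and analysis makes no exception for these scores: "The primary and secondary outcomes in the two groups will be examined to detect the effect of group allocation on each condition". It goes on: "differences between continuous variables will be analysed using Student’s" t-test, with Mann-Whitney U for skewed data and a two-sided 5% level. It also promises an effect size with its precision for each primary and secondary outcome. No paired or nurse-level method is named.

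**Who uses what.** Randomization, concealment, and group allocation procedures assigns individual patients 1:1, with ward nurses at each hospital obtaining the allocation. Under Interventions: "In arm A, nurses use the double-chamber syringe and the traditional syringes will be used in arm B". No separate nursing team per arm is described.

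**The concern.** The two tests named treat the scores in the two arms as independent samples. That suits a patient's score, because patients are randomised. A nurse's score is different. With individual randomisation inside each orthopaedic department, a nurse will normally meet patients of both arms and so give opinions formed on both syringes. Scores from one nurse then share that nurse's general tendency to rate high or low, and perhaps that nurse's liking or dislike of the new device.

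At stake is what the trial can say about nurses' acceptance of the device and its perceived safety, which is part of the stated objectives. Leaving the nurse out can hide a real difference or, under narrower conditions, suggest one that is not there. If the form carries no nurse identifier, the structure cannot be recovered afterwards.

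**Working it through.** **Inputs.** From the protocol: 73 patients per arm (Sample size), two-sided 5% level, t-test or Mann-Whitney U. Not in the protocol, hence assumed: the number of nurses (15 or 30), the correlations, the true differences and the rating schedule. The plan gives no figure for the nurse outcomes. Its only calculation concerns occlusion, and it reproduces: the exact one-sided Fisher test at 73 per arm, 0.19 against 0.05, has power 0.8003 and actual alpha 0.0197.

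Scores are scaled to SD 1.

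**Case A: each nurse rates each syringe once (30 nurses, within-nurse correlation ρ).**

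The true variance of the mean difference is 2(1 − ρ)/30. The independent-samples test uses 2/30, so its standard error is too large by 1/√(1 − ρ). The large-sample true size is 2[1 − Φ(1.96/√(1 − ρ))]. The paired test at a difference of 0.5 SD has noncentrality 0.5·√30/√(2(1 − ρ)) on 29 degrees of freedom.

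| ρ | SE ratio | True size | Noncentrality, paired | Power, paired | Power, independent (simulated) |
|---|---|---|---|---|---|
| 0.3 | 1.20 | 0.019 | 2.32 | 61% | about 47-48% |
| 0.5 | 1.41 | 0.006 | 2.74 | 75% | 47% |
| 0.7 | 1.83 | 0.0003 | 3.54 | 93% | about 47% |

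Simulation with 30 nurses gives slightly larger sizes than the large-sample formula, but still about 2% at ρ = 0.3 and below 0.1% at ρ = 0.7.

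**Case B: one rating per patient, nurses differ only in overall level.**

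Randomisation spreads each nurse's level over both arms. The t-test standard error, √(2/73) = 0.166, is then about right: with ICC 0.3 to 0.5, simulated size is 0.044-0.058 for 15 to 60 nurses. What is lost is precision. If nurse is accounted for, the standard error approaches √(2(1 − ICC)/73), that is 0.138 at ICC 0.3 and 0.117 at ICC 0.5, less what is lost through uneven splits within nurse. At a true difference of 0.4 SD with 15 to 30 nurses, simulated power is about 67-68% for the t-test against 73-90% with nurse accounted for.

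**Case C: as B, but nurses also react differently to the syringe.**

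Assume a nurse variance of 0.3, a nurse-by-syringe variance of 0.2 and a residual of 0.5. With J nurses assigned at random to ratings, the variance of the arm difference is approximately

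2·0.2·[1/73 + (72/73)/J] + 2·0.5/73 + 2·0.3·(1 − 1/J)/73.

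- J = 15: 0.0318 + 0.0137 + 0.0077 = 0.0532, so the true SE is 0.231. The t-test reports about 0.162 (ratio 0.70). Size ≈ 2[1 − Φ(1.977 × 0.70)] ≈ 16-17%.
- J = 30: 0.0186 + 0.0137 + 0.0079 = 0.0402, so the true SE is 0.201. The t-test reports about 0.163 (ratio 0.81). Size ≈ 2[1 − Φ(1.977 × 0.81)] ≈ 11%.

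Simulation gives about 16% and 11%.

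**Case D: only the new syringe is rated.** There is no score in arm B, so no between-arm test can be done.

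**The case against.** A reader might infer that the planned standard errors and p values are wrong however the ratings are collected. The documents do not support that, and the strongest objections are these.

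- **Per-patient ratings may be what is meant.** Interventions says that at the final unblinded visit ward nurses assess all outcomes except insertion attempts and patient satisfaction. If that covers the nurse questionnaire, ratings are per patient, and with only a nurse-level effect the t-test keeps its size (Case B). This stands. The cost is then lost precision, and the test remains valid.
- **The inflated error rests on added assumptions.** Nothing in the protocol gives a nurse-by-syringe variance or a number of nurses. If the question concerns only the participating nurses, with interactions averaging zero over them, simulated size is 0.046-0.054. This stands too, so Case C is conditional.
- **There may be no arm comparison.** Objectives speaks of satisfaction with the medical device, which can mean the new syringe alone. Outcomes speaks of the clinical treatment, and promises only means and SDs. This also stands, but the general analysis paragraph, as written, would still demand a between-group test.
- **Shared nurses are inferred.** No sentence says that the same nurses use both syringes. That is right, but individual randomisation within wards makes it very probable.
- **This is a condensed article.** The assessment schedule and the questionnaires are not shown, and the form may already carry a nurse code. The timing of ratings is therefore no omission to complain of. The article does, however, name the tests and apply them to all secondary outcomes, and that is a stated choice. The t-test is not called independent-samples in so many words, but the two-group wording and the Mann-Whitney alternative leave no other natural reading.

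**Conclusion.** The point holds in a conditional form. As written, the plan compares nurse-reported scores between arms by tests that leave out the nurse. Wherever there is an arm comparison and nurses rate in both arms, an analysis that accounts for nurse fits better:

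- **One rating per syringe:** the planned test is too conservative, with true size 2% down to below 0.1% and power about 47% against 61-93%.
- **One rating per patient, nurse level only:** size is right, and power is about 67-68% against 73-90%.
- **One rating per patient, nurses reacting differently, inference to nurses in general:** size is about 11-16% at an assumed interaction variance of 20%.

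These figures rest on assumed nurse numbers, correlations and differences, and on nurses using both syringes. The documents do not support a claim that the planned p values are wrong under every schedule, or that false positives are the expected result. The matter touches one group of secondary outcomes, leaves the primary outcomes and the sample size alone, and should be settled before recruitment because it affects the form.

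**What to change.** In the analysis section, exempt the nurse-reported outcomes from the general two-group tests, state who completes the questionnaire, how often and about which syringe, and choose accordingly:

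- **Each nurse rates both syringes once:** paired t-test or Wilcoxon signed-rank test.
- **Ratings are per patient:** mixed model with nurse as a random effect, adding nurse-by-syringe variation where it can be estimated. A nurse intercept alone does not deal with Case C. Say whether inference is to the participating nurses or to nurses in general.
- **Only the new device is rated:** descriptive summary, with no between-arm test.

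Bring the Objectives and Outcomes wording into line on what is being rated, and make sure that the questionnaire carries an anonymous nurse code. The cost is a sentence or two, one form field and slightly more analysis work, with no extra patients or visits.
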